## Abstract

Diarrhea, soil-transmitted helminth infection and malnutrition are leading causes of child mortality in low- and middle-income countries (LMICs). To reduce the prevalence of these diseases, effective interventions for adequate water, sanitation, and hygiene (WaSH) should be implemented. This paper describes the design of a cluster-randomized controlled trial that will compare the efficacy of four school-based WaSH interventions for improving children’s health literacy, handwashing, and nutrition. Interventions consisted of (1) WaSH policy reinforcement; (2) low-, medium-, or high-volume health education; (3) hygiene supplies; and (4) WaSH facilities (e.g., toilets, urinals, handwashing basins) improvements. We randomly allocated school clusters from the intervention arm to one of four groups to compare with schools from the control arm. Primary outcomes were: children’s health literacy, physical growth, nutrition status, and handwashing prevalence. Secondary outcomes were: children’s self-reported health status and history of extreme hunger, satisfaction with WaSH facilities, and school restrooms’ WaSH adequacy. We will measure differences in pre- and post-intervention outcomes and compare these differences between control and intervention arms. This research protocol can be a blueprint for future school-based WaSH intervention studies to be conducted in LMICs. Study protocols were approved by the ethics committees of the University of Bonn, Germany, and the University of the Philippines Manila. This trial was retroactively registered, ID number: DRKS00021623.

## 1. Introduction

### 1.1. Background

Malnutrition, characterized by an imbalance in energy and/or nutrient intake [1], affects ~1 out of 3 people globally [2]. In 2017, 22.2% (150.8 million) of all children <5 years old were stunted [3]. In the same year, while 5.6% (38.3 million) children were overweight, 7.5% (50.5 million) were wasted [3], i.e., acutely undernourished or having low weight-for-height < –2 standard deviation (SD) of the World Health Organization (WHO) Child Growth Standards median [4]. Undernutrition, which is highly prevalent in low- and middle-income countries (LMICs), caused 45% (>29,000) of all deaths in children <5 [5,6]. Overweight and obesity caused ~7% (4 million) of all deaths and 120 million healthy years of life lost (disability-adjusted life years [DALYs]) [6]. Malnutrition, in all its forms, could cost society 5% (US $3.5 trillion) of the global gross domestic product (GDP) [7]. High economic losses disproportionately affect LMICs. Child undernutrition alone cost US $7 million and US $254 million in Swaziland and Uganda, respectively [8].

Preventing children’s malnutrition involves preventing infectious diseases that precipitate imbalanced energy and/or nutrient intake. Diarrhea and soil-transmitted helminth (STH) infections, which affect millions of children in LMICs [9,10], can be prevented by interrupting routes of fecal-oral disease transmission through practicing proper hygiene, especially handwashing, handling food and disposing waste safely, and providing access to clean water for drinking and washing. Interventions for improving water, sanitation, and hygiene (WaSH) have been associated with decreased risk of diarrhea and STH infections, and consequently, decreased risk of malnutrition in various community settings [11,12]. For example, a cluster-randomized controlled trial (cluster-RCT) conducted in rural India found that the construction and promotion of latrines was associated with decreased diarrhea prevalence and increased weight-for-age z-score in children [11]. In Bangladesh, a cluster-RCT showed that an intervention incorporating water quality, sanitation, handwashing, and nutrition was associated with decreased diarrhea and increased height in children [12]. In 2016, 6000 deaths due to malnutrition could have been prevented by improving WaSH [13]. However, it is unclear how WaSH interventions in schools benefit children in LMICs, specifically in megacities, i.e., cities with >10 million inhabitants [14].

The Philippines, an archipelagic country in Southeast Asia, had a population of ~106.7 million in 2018 [15]. The Philippines’ National Capital Region, known as Metro Manila, is identified as a megacity although it is not a single city but a metropolitan area comprising 16 cities. Metro Manila had ~12.9 million inhabitants in 2015 [16], representing 12.1% of the country’s total population. In 2015 Metro Manila’s population density was 20,785 persons per km^2^ [17], or more than 4 times the population density of Beijing in 2014 [18]. Compared to other cities in LMICs, Metro Manila has a unique risk profile as a megacity that is exposed to ≥3 types of natural disasters [14], e.g., typhoons, floods, and volcanic eruptions. Thus, Metro Manila represents an important intersection of human health and the environment. Gaps in environmental health management have contributed to the increased prevalence of environment-related infectious diseases such as diarrhea and STH infections, making Metro Manila a precarious area to live in. This is an important issue because of long-term health consequences, e.g., growth stunting [10]. In 2018 more than half (53.9%) of households in the Philippines was food insecure [19]. In the Philippines the average daily intakes of whole grains and milk (45.5 g/day and 3.7 g/day, respectively) are lower compared to those in Indonesia (51 g/day and 7 g/day, respectively) [3]. Prevalence rates of school-age children’s (6–10 years old) stunting, underweight, wasting/thinness, and overweight-for-height were: 24.5%, 25%, 7.6%, and 11.7%, respectively [20]. In the Asia region, the average stunting rate for children <5 years old is 21.8% but in the Philippines it is >30% [3]. The prevalence of low birth weight is higher in the Philippines (20%) compared to Ghana (14.2%) [3]. The prevalence of wasting for children <5 years old in the Philippines (5.6%) is higher than in Malawi (1.3%) [3]. While undernutrition alone is estimated to cost the Philippines USD $4.5 billion annually [21], the overall cost of hunger was USD $6.5 billion in 2013 [22].

The Philippines Department of Education (DepEd) oversees 54,602 public schools nationwide, hosting >22.6 million children during the School Year 2018–2019 [23]. While public schools receive government funding, they suffer from a lack of teachers and classrooms, and therefore, are overcrowded. The student-to-classroom ratio in Metro Manila public schools ranges from 50:1 to >100:1 [23,24]. This shortage of classrooms has caused the implementation of “double-shift” school-days, wherein one-half of students attend school during a morning shift (6:00 a.m.–12:00 p.m.) and another half attend school during an afternoon shift (12:00 p.m.–6:00 p.m.). The country’s poorest children attend public schools. They are vulnerable to contracting diarrhea and STH infections because they are usually malnourished due to their low socioeconomic status (SES). The school environment, which they are regularly exposed to for prolonged periods, possibly plays a major role in this. Policies have been implemented to achieve adequate WaSH in schools (Box S1), yet there remain sizable gaps in WaSH management--gaps, which threaten the status of schools as health- and education-promoting environments and increase children’s risk of disease.

### 1.2. Objectives

The WaSH in Manila Schools Trial aimed to identify an intervention that could better improve children’s health. Our conceptual framework (Figure 1) depicts our pre-specified hypotheses (Figure 2). To test our hypotheses, we will compare a comprehensive school-based WaSH intervention with no intervention, rather the “standard of care”. This comparison will enable us to estimate a potentially achievable reduction of inadequate WaSH, as well as estimate impacts on malnutrition reduction. Through our description of exposure-response relationships in Metro Manila schools, we will be able to provide estimates of the range of improvements that can be achieved in real-world, LMIC conditions where elements of adequate school WaSH, including improved sanitation, are typically combined with inadequate school WaSH and unimproved sanitation. Results of the trial will be reported in a forthcoming paper (unpublished; manuscript in preparation) [25]. In this paper, we present and discuss the rationale and design of a cluster-randomized controlled trial (RCT) that tested the efficacy of a school-based WaSH intervention. The research protocol we describe in this paper was designed and implemented in the Philippines but it can serve as a blueprint for conducting future intervention studies in other LMICs.

## 2. Research Methodology

### 2.1. Study Overview and Design

WaSH in Manila Schools was a research project aimed at improving children’s environmental health by addressing inadequate school WaSH and promoting health literacy and hygiene practices (Figure 2). We implemented the project from January 2017 to February 2019, first conducting an observational study [27] to assess the WaSH situation in 15 public schools in Metro Manila, and then conducting a longitudinal study to develop, implement, and evaluate WaSH interventions in the same public schools (Figure 2). We conducted a cluster-RCT to address three specific aims (Figure 2) and compare the efficacy of four school-based WaSH intervention packages. Each intervention package consisted of different combinations of four elements: (1) WaSH policy reinforcement, (2) health education, (3) hygiene supplies, and (4) WaSH facilities (e.g., toilets, urinals, handwashing basins) improvements (Table S1).

This was a two-arm cluster-RCT (Figure S1), with one intervention arm and one control arm. The control arm received no intervention, rather the “standard of care”, which we defined as WaSH policy reinforcement, a hygiene workshop for teachers, and two health education sessions. The intervention arm was further divided into four groups (A, B, C, and D), based on the volume (low, medium, or high) of health education provided. Cluster units were public schools located in three cities of Metro Manila, Philippines, where many people, including a majority of public school children, were exposed to inadequate WaSH.

### 2.2. Study Population

For primary schools, we recruited students in grades 5 and 6 and for secondary schools in grades 7 and 10. These grade levels were chosen because we wanted to involve students who were: (1) developmentally mature enough to use and have perceptions about school WaSH facilities; (2) capable of responding independently or with minimal assistance to our questionnaire using a tablet or smartphone; and (3) able to actively participate in intervention activities (for inclusion and exclusion criteria for students, see Table S2).

### 2.3. Sampling and Recruitment

We conducted formative research (Figure S2) to prepare for the implementation of our intervention. We previously described how we estimated the sample size using the Lynch formula [27]. The target population was all the public school children in Metro Manila, where in School Year 2014–2015 a total of 2,059,447 public school children (1,373,852 elementary and 685,595 secondary school children) were enrolled [23]. We inflated the sample by 30% and 45% to account for nonresponse and refusal, respectively, and then inflated the sample by another 5% to account for differences in schools’ enrollment sizes. The target sample size was N = 760; we enrolled 756 students at baseline and 703 students at the 8-month follow-up (retention rate: 86%) (Figure 3).

We selected schools located in Manila, Navotas, and Quezon City (Figure 4) because they were geographically and demographically representative of cities in Metro Manila. We recruited the school principals from the 15 public schools that participated in our previous observational study [27]. We used convenience, rather than probabilistic, sampling, choosing to revisit the same 15 schools because of existing relationships of trust and cooperation with school principals and personnel. These factors can facilitate communication and collaboration, which were crucial because we aimed to maintain a long-term working relationship with schools in spite of our limited resources in time, personnel, and materials. We previously described our multi-stage cluster sampling strategy [27]. Based on the school’s enrollment size, 1–2 class sections were selected to obtain a target sample of ~50 students per school. We recruited entire class sections as a whole rather than groups of students from multiple class sections so as not to interrupt on-going classroom instruction with our research activities. We decided not to re-recruit the students from our previous observational study as a new school year had begun, resulting in students advancing up to the next grade level (e.g., from grade 5 to 6) and moving to different class sections, as well as some students transferring to different schools that were not involved in our study. No monetary reimbursement was offered to school principals, and all schools were compensated (Table S6) with printed research portfolios, certificates of appreciation, classroom viewings of an educational film promoting handwashing, and hand hygiene gel.

### 2.4. Ethics Approval

The ethics committees of the University of Bonn, Germany (Number 216/16), and the University of the Philippines Manila (Number 2017–0113) provided written approvals for the study. Before conducting the school surveys we obtained written approval from the DepEd through division superintendents. Written informed consent was provided by school principals in loco parentis, i.e., in the place of a parent, for the children’s participation. Prior to conducting our study, we described to the children the study procedures in an easy to understand way using the local language (Filipino/Tagalog). We emphasized that participation in our study was voluntary and that anyone could decide to stop participating in the study anytime. We encouraged children to ask the research team any questions they might have. We accepted children’s affirmative agreement (“assent”) to participate in the study as soon as they actively showed a willingness to join the research project by completing the questionnaire and undergoing a health examination. We retroactively registered our study in the German Clinical Trials Registry (DRKS), ID number: DRKS00021623. Study registration was delayed due to logistical and human resource constraints. We strictly followed the protocols, which were developed before data collection. This ensured that the study’s quality was not impaired.

### 2.5. Data Collection

#### 2.5.1. Assessing Primary Intervention Outcomes

First we assessed children’s health literacy, measured by two continuous variables (hygiene literacy and handwashing literacy scores) via questionnaire (Tables S3 and S4). Second we assessed child growth, measured by continuous variables (z-scores for height-for-age [HAZ] and body mass index-for-age [BAZ]) and binary variables (prevalence of malnutrition [stunting, undernutrition, and overnutrition]), via anthropometry (Table 1). HAZ is a linear growth indicator that indicates if the child has the appropriate stature for his/her age, while BAZ is an indicator of growth that indicates if the child has the appropriate ratio of weight and height for his/her age, according to WHO guidelines [4,29,30,31,32]. We used the WHO AnthroPlus (for children 5–19 years old) software (version 3.2.2., WHO, Geneva, Switzerland) to obtain HAZ and BAZ for each child. Third we assessed handwashing prevalence via observation according to standard operating procedure (SOPs) (Figure S3).

#### 2.5.2. Assessing Secondary Intervention Outcomes

First we assessed children’s overall health status, extreme hunger prevalence, and satisfaction with and perceived cleanliness of schools’ WaSH facilities, measured by binary variables, via questionnaire (Table S6). We assessed acute dehydration, measured by incidence of highly concentrated urine (U_sg_ ≥ 1.020) [33,37,38] (Table 1), via urinalysis using urine test strips (Insight Urinalysis Reagent Strips, Acon Laboratories Inc., San Diego, CA, USA). Urine test strips are an affordable, easy to use, and reliable way to perform urinalysis in field settings [39]. Second we assessed school principals’ satisfaction with schools’ WaSH facilities and children’s hygiene practices, measured by binary variables, via interview. Third we assessed, via observation, schools’ WaSH adequacy, measured by continuous and binary variables describing availability, accessibility, cleanliness, and functionality, according to guidelines from the Philippines DepED and Department of Health (DOH) [35,40]. We previously reported the data collection tools we used for conducting health examinations, interviews with school principals, and school restroom inspections [27]. Data collection tools were pilot-tested and improved prior to beginning this trial.

During our previous observational study, we found that children were avoiding or not using school restrooms, possibly due to a perceived lack of cleanliness or lack of privacy. Findings indicated that avoidance and non-use of school restrooms increased children’s risk of diarrhea. Thus, we aimed to see if our intervention was effective in improving children’s perceptions about school restrooms, with the hope that children would use school restrooms rather than avoid using them. Also, we found that school WaSH policies were in place, yet school principals reported being unsatisfied with WaSH facilities and children’s hygiene behaviors. School principals’ perceptions about WaSH could affect efforts to implement, maintain, and sustain improvements, all of which influence children’s health and hygiene behaviors. Thus, we aimed to see if our intervention was effective in improving school principals’ perceptions about school WaSH facilities.

#### 2.5.3. Baseline Survey and Randomization

At baseline, we conducted a four-part school-based survey (Figure S3) to measure: (1) children’s health literacy and nutrition status; (2) handwashing prevalence; (3) school restrooms’ WaSH adequacy; and (4) schools’ WaSH policies. We developed a self-administered health literacy questionnaire for children in English and then translated it to Tagalog (Filipino language) (Tables S3 and S4). We made one version for primary and one version for secondary school children. The QuickTapSurvey^©^ app (Formstack LLC, Fishers, IN, USA), installed on password-protected tablets and smartphones, was used to administer all survey instruments. It is a cloud-based data collection tool that allows for simultaneous offline data entry and stamping with global positioning system (GPS) coordinates, date, and time. We applied validation rules and range limits for precise data entry.

The research supervisor conducted a full-day (8 h) initial training workshop (Table S7) for research assistants before conducting school surveys. Each school survey was conducted by a team of 5–7 rotating research assistants, directly managed by the research supervisor. To begin the school survey, we first explained the study’s aims, objectives, and methods to the children in Tagalog (Figure S3). We emphasized that participation in our study was voluntary and anonymous, and that results would remain confidential and have no impact on anyone’s school grades. Children’s full name, date of birth, and telephone number were collected and stored in a separate Microsoft© Excel spreadsheet secured in password-protected tablets. Next, we assigned children unique identification (ID) numbers and gave them each three tickets that were printed with their ID number. The ticketing system was a quality control measure that ensured that all children provided all the requested data. Children were instructed to give one ticket to the assigned research assistant at every station that they visited during the school survey (Figure S3).

After obtaining data from the children, research assistants completed the school restroom inspection checklist, took photos of WaSH facilities, and interviewed school principals or representatives, inputting all data into the app. We obtained school administrative data, e.g., budget for maintenance and other operating expenses, from the DepEd. At the end of each workday, research assistants discussed their work with each other, shared lessons learned, and identified areas for improvement. Upon accessing an internet hotspot, we used the app to transmit anonymized data to a central database via cloud storage. Research assistants periodically checked uploaded data to verify the completeness of data upload and identify discrepant, missing, or duplicate data. When needed, appropriate remedial action was taken, e.g., re-training research assistants or clarifying instructions for children.

After completing baseline surveys, we assigned two schools to the control arm and 13 schools to the intervention arm (Figure 3). We purposefully assigned two schools to the control arm because one school had a school principal who directly asked us to participate in our previous observational study. The other school was integrated (offering all possible grade levels, from kindergarten to grade 12) and was the location where we had pilot-tested our survey instruments before the observational study. We randomly allocated schools in the intervention arm to one of four groups. One research assistant and the research supervisor conducted randomization in Microsoft^©^ Excel as follows: (1) In one column, we listed the names of the 13 schools in the intervention arm, with one row representing one school. (2) In another column, we listed the four intervention groups (A, B, C, and D), with one row representing one group. We previously determined how many schools would be allocated to each group (Table S1). (3) In a third column, we used Excel’s random number function and ranked the schools, assigning each school to either group A, B, C, or D (Table S1). Except for the research supervisor, all research assistants, study participants (children), school personnel, and parents were blinded to the assignment of schools to the intervention arm and subsequent random allocation to intervention groups A–D.

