At the core of our intervention was health education. Research assistants conducted interactive verbal presentations for children, who, depending on which intervention group they belonged to, received two to four health education sessions that lasted one hour each. The content of the health education sessions (Figure S5) was based on the existing DepEd curriculum and open educational resources from, e.g., the United States Centers for Disease Control and Prevention (CDC) and Environmental Protection Agency (EPA). Microsoft^©^ PowerPoint slides, with visually appealing graphics to attract children’s attention, were created (Figure S5). Each health education session included a brief lecture, class discussion, and a trivia game. We also incorporated role-playing, other games, and singing the “Happy Birthday” song to teach children the correct duration of time for handwashing. Besides health education sessions, we used mixed methods to pique children’s interest, invite active participation, and encourage a sense of empowerment about hygiene at the personal- and environment-levels. For example, we implemented poster-making and school restroom-cleaning contests, as well as songwriting workshops specifically for children and adolescents from secondary schools. Research assistants also developed an original educational video, filmed in Tagalog, called “Hygiene Heroes”, to promote proper handwashing (Film S1). After launching the intervention, we promoted adherence with various communication strategies (Table S8).

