### 2.8. Statistical Analysis

Because our study contains multiple arms (1 control and 4 intervention arms), it is necessary to develop a strategy for conducting statistical analysis that takes into account the study’s 5 arms, parallel design, and unequal allocation ratio between control and intervention arms. We will use an adjustment method to control for type I error due to the study’s multiple-arm design. Because we simultaneously assessed multiple outcomes, we will need to adjust for a possible multiple comparisons effect. One possible adjustment method is the Benjamini–Hochberg procedure [42], which controls for the false discovery rate (10%). We used unequal allocation, making the intervention group larger than the control group, because we aimed to increase the precision of the intervention comparison. Also, we aimed to make the study more acceptable to study participants and researchers by decreasing the likelihood of being allocated to the control group and not receiving the intervention. Because we aim to know whether and how interventions differ, we will not use a single global test of significance, which would compare all groups simultaneously. Rather we will use a dose-response model to examine trends. We will conduct all analyses by using the originally assigned intervention status (i.e., intention to treat), comparing each intervention arm against the control arm.

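### The comparison with control is not randomised, because the two control schools were hand-picked, so the cluster-RCT label and the allocation rationale need correcting

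*Protocol article*

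**What the plan says.** **Assignment (Section 2.5.3).** "After completing baseline surveys, we assigned two schools to the control arm and 13 schools to the intervention arm". The control schools were not drawn by lot: "We purposefully assigned two schools to the control arm because one school had a school principal who directly asked us to participate" in the previous observational study. The other control school was integrated, from kindergarten to grade 12, and "was the location where we had pilot-tested our survey instruments before the observational study". A random number in Excel then placed the remaining 13 schools in groups A to D. The group sizes are in Table S1, which is not shown.

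**Label and contrasts.** Section 2.1 calls the study a two-arm cluster-RCT with one intervention arm and one control arm. Section 2.8 says all analyses follow original assignment (intention to treat), "comparing each intervention arm against the control arm". Section 2.5.4 (change scores) and Section 2.8.2 (t-test, Poisson regression, GLMM) use the same contrast. Section 2.8 also mentions a dose-response model for trends and does not say whether control is one of its levels.

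**Rationale for the unequal split (Section 2.8).** Two reasons are given: to raise the precision of the intervention comparison, and to make the study more acceptable "by decreasing the likelihood of being allocated to the control group and not receiving the intervention".

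**Content of control.** Sections 1.2 and 2.1 speak of no intervention but equate it with a standard of care, "which we defined as WaSH policy reinforcement, a hygiene workshop for teachers, and two health education sessions". Children in the intervention groups "received two to four health education sessions that lasted one hour each" (Section 2.6). All schools were compensated with items that included "classroom viewings of an educational film promoting handwashing, and hand hygiene gel" (Section 2.3).

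**Disclosure.** The Discussion lists the lack of randomisation to control or intervention as a limitation, and the implications section recommends it for future studies.

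**The concern.** Random assignment of clusters is what lets a difference between arms be read as the effect of the intervention, with an error rate that can be stated. Here it covers A against B against C against D. It does not cover intervention against control, which is the contrast that Section 1.2 uses to test the hypotheses and that the main efficacy estimates target.

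The way control was chosen could matter. Section 2.5.2 argues that principals' perceptions shape WaSH efforts and, through them, children's health and hygiene. One control school was picked because of what its principal did. The other differs in school type and had earlier contact with the survey instruments. The article states no link to outcomes, so the direction of any bias is unknown.

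At stake is the wording of the main conclusion. A difference from control reported as a cluster-RCT result, analysed by intention to treat, would be read as a randomised effect against no intervention. It is neither randomised nor against no intervention. The article also offers itself as a blueprint, so the mislabelling could be copied.

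**Working it through.** **Inputs from the article:** 2 control and 13 intervention schools (2.5.3); 703 children at follow-up (2.3), so 703/15 = 46.9 per school; two-sided tests (2.8.2).

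**Assumed, because not shown:** alpha 0.05; 80% power; intraclass correlation (ICC) 0.01 to 0.10 for the analysed outcome; groups A to D of 3 or 4 schools.

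**1. The article's own size figure.** The target of 760 is the only one. The Lynch formula with N = 2,059,447 and assumed z = 1.96, p = 0.5, d = 0.05 gives 384.1, and 384.1 × 1.30 × 1.45 × 1.05 = 760.2. It therefore reproduces as the precision of one prevalence. It involves no contrast between arms and cannot support the precision argument for 2:13.

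**2. Was chance involved?** There are C(15,2) = 105 ways to choose two control schools. The realised pair was chosen for stated reasons, so it has no randomisation distribution and no likelihood of control allocation existed to be lowered.

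**3. Precision of 2:13.** With equal school-level variance, the variance of the difference is proportional to 1/k1 + 1/k2.
- 2 v 13: 1/2 + 1/13 = 0.577
- 7 v 8: 1/7 + 1/8 = 0.268
- Ratio: 0.577/0.268 = 2.15

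For one group against control the loss is smaller. Relative to 3 v 3 (1/3 + 1/3 = 0.667), 2 v 3 gives 0.833/0.667 = 1.25 and 2 v 4 gives 0.750/0.667 = 1.125. If the sentence in Section 2.8 refers to comparisons among A to D, having 13 schools there does help, but the sentence does not say so.

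**4. How far two schools can move the estimate.** The school-level standard deviation of the 2 v 13 difference, in outcome SD units, is √(ICC × 0.577). The 95% range is ±1.96 times this: ±0.15, ±0.33 and ±0.47 SD at ICC 0.01, 0.05 and 0.10. That is ordinary between-school variation, before any selection.

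**5. What the randomised part can support.**
- Four groups of 4/3/3/3: 13!/(4!3!3!3!) = 1,201,200 allocations for a global test.
- Four groups share three education volumes, so a trend has fewer distinct allocations, for example 13!/(7!3!3!) = 34,320. That is still ample for a permutation test.
- Pairwise: 3 v 3 has a minimum two-sided p of 2/20 = 0.10, and 3 v 4 of 2/35 = 0.057. Neither can reach 0.05.

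**6. Detectable differences** (school-level t, noncentral, in SD):

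| ICC | 2 v 13 | A–D trend, high minus low, three assumed layouts |
|---|---|---|
| 0.01 | 0.41 | 0.35–0.41 |
| 0.05 | 0.61 | 0.52–0.62 |
| 0.10 | 0.80 | 0.68–0.81 |

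The two are similar in size, although they answer different questions.

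**The case against.** The article is open about this. The abstract says that schools within the intervention arm were randomised, Section 2.5.3 gives the method and reasons, and the Discussion names the bias. Section 2.8.2 plans adjustment for baseline differences between the arms, and pre-post differences remove stable differences in level between schools. All 15 schools were a convenience sample in any case. These points stand as mitigation, and there is no concealment. They correct neither the label nor the rationale. The listed example confounders are child and household factors, and differencing does not remove a different trend in two particular schools.

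Several stronger readings are tempting, and the documents do not support them:
- *Every efficacy comparison rests on the control schools.* The trend in Section 2.8 could be fitted within A to D, and the Conclusions speak of comparing impacts across education volumes.
- *No model could ever separate school and intervention effects.* The article supports only that the planned models, with two control clusters, cannot.
- *Control is coded as dose zero.* This is written nowhere. The film and gel went to all schools, so they are common to both sides.
- *The randomised comparison has over a million allocations while the control comparison has 10 or 15.* That sets a global count against a pairwise one. The pooled control count would be 105, and a 3 v 3 comparison within A to D also has a floor of 0.10.
- *The confirmatory claim should move to A to D.* That leaves the standard-of-care question in Section 1.2 unanswered. It would also be a switch made after fieldwork ended in February 2019 (2.1) and preliminary results were presented (2.7.2).

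**Conclusion.** The concern holds, limited to the comparison with control. That comparison is non-randomised, yet the design label, the intention-to-treat framing and the allocation rationale present it as if it were randomised. The statement about the chance of control allocation is incompatible with Section 2.5.3. The precision argument is wrong for the pooled control contrast by a variance factor of 2.15 against 7:8, which needs only the two school counts and equal school-level variance. Chance differences between schools of about ±0.33 SD rest on an assumed ICC of 0.05. The permutation floors rest on assumed group sizes of 3 or 4.

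The contrast also estimates an effect beyond policy reinforcement, a teacher workshop and two sessions. Two is also the lowest session count given for the intervention groups. The correction is needed before results are reported because it changes what may be concluded. It does not make the control comparison worthless, and it does not require a different primary question.

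**What to change.** 1. Describe the study as randomised among intervention groups A to D with a non-randomised control, in the abstract, Section 2.1 and Section 2.8.
2. Keep the control contrasts, which address the question in Section 1.2. Report them as non-randomised, baseline-adjusted comparisons with two control clusters, without a causal claim that rests on randomisation.
3. Delete the rationale about the chance of control allocation. Delete the precision rationale, or restrict it to comparisons among A to D.
4. Describe the control contrast as the effect beyond policy reinforcement, teacher workshop and two sessions. If control enters the dose-response model, state that it is not dose zero.
5. Report, as the only randomised comparison, one school-level trend or global test across the 13 schools with permutation inference, labelled as specified after fieldwork. Section 2.8 currently rules out a single test across all groups, so a global test would need that sentence amended. Treat pairwise A to D tests as supportive. Read a trend in sessions together with the other package elements that differ between groups.

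The cost is rewording plus one added analysis, with no new data. The real price is weaker causal language for the comparison with control.
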